**Summary**

**Context**

Melarsoprol is the most commonly used product for the treatment of patients suffering from human African trypanosomiasis (HAT) in the meningo-encephalitic phase. This treatment is frequently complicated by fatal reactive encephalopathy, and at the same time resistance is beginning to appear in various countries. Eflornithine is effective and better tolerated, but its availability is not guaranteed and it is difficult to use. Nifurtimox, a treatment of Chagas' disease but used in the 1980s in series of cases of HAT, is at present the only other potential candidate for the treatment of late-stage HAT.

The limited number of compounds available, the lack of prospects for the development of new products and the emergence of resistance are arguments for the use of therapeutic combinations. In addition, drug combination should reduce the dosages of the drugs used and hence improve their safety. These new protocols, however, must be validated in terms of therapeutic efficacy and clinical safety. Three therapeutic combinations are nowadays possible: [melarsoprol + nifurtimox], [melarsoprol + eflornithine] and [eflornithine + nifurtimox].

**Main objective**

To compare the following 3 therapeutic combinations in terms of therapeutic efficacy and clinical safety: A: [melarsoprol + nifurtimox], B: [melarsoprol + eflornithine] and C: [eflornithine + nifurtimox] in patients suffering from *Tbg* HAT in the meningo-encephalitic phase.

**Methods**

Randomised, open, clinical equivalence trial. The criteria of assessment will be based on the proportion of therapeutic failures in each of the groups, itself based on the presence of trypanosome(s) in the CSF, blood or lymph node fluid, and on spinal cell count. The second outcome variable will be the proportion of side effects occurring in each treatment group. The third outcome variable will be the duration of survival without signs of parasitic infestation for 24 months after treatment.

The study will be conducted in Northern Uganda.

**Study duration**

36 months

**Institutions involved**

- Ugandan National Sleeping Sickness Control Program
- Médecins sans Frontières
- Epicentre

**Introduction**

*Trypanosoma brucei gambiense* (*Tbg*) Human African Trypanosomiasis (HAT) is a major public health problem in those areas in which it is currently rife (1). This is all the more so because the political upheavals, which disrupt the operations of the health services and cause population movements encourage the reappearance of historical foci (2,3). This disease, however, is still neglected and it is estimated that the control programmes cover only 10 to 20% of the 50 million people living in endemic regions (2).

HAT, which is consistently fatal in the absence of treatment, respond to a relatively non-toxic therapeutic agent, pentamidine(Pentacarinatâ), if the diagnosis is made at the hemo lymphatic phase (4). In the late stage of the disease, however, when the central nervous system is invaded by the parasite, use of arsenic derivatives such as melarsoprol (Arsobalâ) remains necessary. In about 5% of cases the use of melarsoprol causes iatrogenic encephalopathy, with a fatal outcome in up to 50%.

Eflornithine (difluoromethylornithine or eflornithine, Ornidylâ), for the time being, is the only other drug registered for the treatment of late-stage HAT. The institution of treatment regimens with eflornithine, however, is difficult because of the mode of administration of the product (1 infusion of 2 hours, every 6 hours). Actually, eflornithine is no longer available on the market but the patent is under supervision of WHO (5).

Nifurtimox (Lampitâ, Bayer), a product used in the treatment of Chagas disease, has only been tested empirically in HAT with contradictory results (4,6,7). This is a cheap drug, which is easy to administer (orally) but not registered for use in HAT. The type and frequency of side effects are poorly documented.

The available therapeutic spectrum for the treatment of late-stage HAT is therefore limited. Furthermore, the availability of the 3 drugs listed here is only guaranteed in the medium-term. Finally, signs of resistance to melarsoprol are beginning to appear in several areas (8,9).

The search for new approaches to the therapeutic management of late-stage HAT is therefore necessary. The limited number of compounds available, the lack of prospects for the development of new products and the emergence of resistance are arguments for the use of therapeutic combinations. In addition, the use of synergistic drug combinations in time would reduce the dosages and hence the hospitalisation period and the incidence of side effects. These new protocols, however, must be validated in terms of therapeutic efficacy and clinical safety. Three therapeutic combinations are possible today: [melarsoprol + nifurtimox], [melarsoprol + eflornithine] and [eflornithine + nifurtimox). We propose to undertake a clinical trial comparing these three combinations in terms of therapeutic efficacy and clinical safety in patients suffering from *Tbg* HAT in the meningo-encephalitic phase.

**1. Context**

**1.1. Current protocols for the treatment of HAT - Toxicity of melarsoprol.**

## Standard protocols

The treatment of HAT depends on the stage at which the disease is diagnosed.

· Pentamidine in the hemo lymphatic phase

Pentamidine isethionate, an aromatic diamine, is the reference drug used for the treatment of early-stage HAT. Patients are hospitalised and receive 4 mg/kg of pentamidine in a daily intramuscular injection for 7 to 10 days.

· Melarsoprol in the meningo-encephalitic phase

The treatment of patients with late-stage disease involves the use of melarsoprol, a trivalent arsenical derivative requiring a more intense protocol and hospitalisation for 25 days. Melarsoprol has been used almost exclusively in the treatment of late-stage HAT for more than 40 years (10). The mode of action of melarsoprol is poorly understood. According to one generally accepted theory (although recently disputed), melarsoprol acts by depriving the trypanosome of trypanothion by binding irreversibly to it. Trypanothion, which is the analogue of glutathion in trypanosomes, protects the parasite from free radicals. The pharmacokinetic of melarsoprol is poorly understood, but it appears that the half-life of the drug is 35 hours. Melarsoprol crosses the blood-brain barrier in limited quantities (10,11).

In a common protocol with Melarsoprol, patients receive three series of three intravenous injections separated by rest periods of six days. The doses of melarsoprol are progressive, from 1.8 to 3.6 mg/kg/day. Prednisolone is combined systematically, as a preventive measure against reactive encephalopathy (12).

A continuous treatment schedule (2.16 mg/kg/day for 10 days) simplifying the protocol and reducing the hospitalisation period is currently under evaluation in several countries. Preliminary results show equivalent efficacy and similar safety to the standard therapeutic regimen (13).

## Results and side effects of treatment with melarsoprol

In the late-stage disease, the cure rate after treatment with melarsoprol is estimated to be greater than 95% (10,11,14). The principal risk is that of reactive encephalopathy (5.9% of cases treated with melarsoprol in a series of 1083 patients in Zaire (15), with a high mortality rate (67.2% in the same series). In an Ivory Coast series with 350 patients (6), arsenical treatment was associated with minor side effects, such as isolated febrile episodes, pruriginous rashes and subcutaneous cellulitis, sometimes followed by necrosis at the injection site, in 11.4, 4.6 and 2.8% of cases, respectively.

MSF data from Adjumani in Northern Uganda provide the following figures: among 3110 late-stage patients treated with melarsoprol, 567 (18.2%) patients suffered side effects, including 194 (6.2%) cases of reactive encephalopathy. The lethality observed during treatment was 5.5% (170/3110). The lethality of reactive encephalopathies was 51.5% (100/194). The median duration of hospitalisation was 25 days (unpublished MSF data).

**1.2. Increase in therapeutic failures with melarsoprol**

In Arua in north-west Uganda, about 25% of cases of HAT treated for the first time with a complete course of melarsoprol result in therapeutic failures (the usual therapeutic failure rate after treatment with melarsoprol is less than 5% (10,14). In addition, repeated courses of melarsoprol in cases that had relapsed initially do not produce a cure in these patients (9,16). An identical phenomenon has appeared in Southern Sudan, in the region of Ibba, where a 6-month relapse rate of 30% has been observed (unpublished MSF data). High relapse rates after treatment with melarsoprol have already been reported in the past, particularly in Zaire (10).

Supplementary analyses on strains circulating in the Arua region have shown that the high therapeutic failure rate observed in this region was due to the appearance of melarsoprol-resistant strains of trypanosomes (17).

This phenomenon, which may extend to other sites, constitutes a major public health problem because of the lack of second-line drugs for the treatment of late-stage HAT.

**1.3. Other drugs used for the treatment of late-stage HAT**

## Eflornithine

Difluoromethylornithine (eflornithine or DFMO) has been the only new molecule introduced in the treatment of HAT over the last few decades. Eflornithine was used successfully in the treatment of late-stage HAT during the 1980s (4,10). It is a trypanostatic drug, which acts as an inhibitor of ornithine decarboxylase (an enzyme acting on the cycle of synthesis of polyamines, which themselves are involved in cell multiplication and differentiation) (10,11). This ornithine decarboxylase inhibition activity also causes a reduction in the synthesis of trypanothion, which would allow a synergistic action between eflornithine and melarsoprol. The half-life of eflornithine is short (3.3 hours) (10,11). Eflornithine readily penetrates the cerebrospinal fluid (CSF) and its concentration in the CSF is higher in adults and patients already treated with melarsoprol, probably because of the greater permeability of the blood-brain barrier (18). This might explain why a lower therapeutic failure rate is observed in patients treated with eflornithine after melarsoprol failure, but with a higher frequency of side effects (unpublished MSF data).

Eflornithine is better tolerated than melarsoprol, even if its prescription causes the occurrence of a number of side effects, all reversible and without consequences on discontinuation of treatment: pancytopenia, diarrhoea (particularly when eflornithine was taken orally), convulsions, hallucinations, insomnia, hearing loss, alopecia. In patients treated with eflornithine after melarsoprol failure, a continuous course of treatment for 7 days (100 mg/kg every 6 hours) appears to have the same efficacy as a 14-day treatment (19).

The availability of eflornithine has become erratic, the manufacturer having discontinued the production process after the recent manufacture of a final batch of product ensuring the short-term availability of the drug. However, the medium-term availability of eflornithine depends on the identification of a new laboratory prepared to take on the production.

## Nifurtimox

Although never having received marketing authorisation for the indication of the treatment of HAT, nifurtimox was used in series of cases with late-stage HAT during the 1980s, particularly in Zaire (7) and Southern Sudan (4), with contradictory results. This product, a 5-nitrofuran normally used in the treatment of Chagas' disease, is an inhibitor of the trypanothion reductase enzyme (10,11).

Nifurtimox has a short half-life, of the order of 3 hours, and must be administered orally every eight hours. In Chagas' disease, the dose of nifurtimox is 10 mg/kg/day divided in 3 doses for 30 days. Some clinicians use higher doses of 15 mg/kg/day in 3 doses for 3 months. In HAT, no treatment schedule to date has been the subject of consensus. The doses used in the past have been fairly variable:

· 120 mg per day in 3 doses for 120 days or 150 mg daily in 3 doses for 60 days in combination with suramin (in adults: i.e. more or less 6 mg/kg/day) (20).

· 4 to 5 mg/kg/day in 3 doses or 12.5 to 15 mg/kg/day in 3 doses for 60 days (18)

· 30 mg/kg/day in 3 doses for 30 days or 15 mg/kg/day in 3 doses for 60 days (7)

· 15 mg/kg/day in 3 doses for 14 to 45 days alone or in combination (20,4).

The most widely used schedule is now 15 mg/kg/day in 3 doses for 2 weeks in adults and 20 mg/kg/day in 3 doses over the same period in children under 15 years of age.

The most commonly observed side effects include anorexia and weight loss, headaches, neurological effects (central: cerebellar syndrome, convulsions, coma, confusion, insomnia, and peripheral: paresthesia, motor deficits), digestive effects (nausea, vomiting, epigastric pain) and skin rashes. The toxicity of nifurtimox appears to increase with the duration of treatment (21).

The availability of nifurtimox in the future is not guaranteed.

**1.4. Drug combinations**

The combination eflornithine + melarsoprol has proved synergistic in a murine model (22) and effective in one human case after 3 ineffective courses of treatment with melarsoprol alone and 1 ineffective course of treatment with eflornithine per os alone (23). There is a rationale for introducing melarsoprol at the end of treatment with eflornithine, as melarsoprol is more active when the trypanothion pool has been reduced by eflornithine (22).

Nitrate derivatives might potentiate the effects of arsenicals at the level of trypanothion.

In RDC, 69 patients have been treated with the combination nifurtimox + melarsoprol. One of them is dead, and no relapse was recorded after 12 months of follow-up ([name], personal communication)

We have no knowledge either of series of cases treated with a combination of nifurtimox + eflornithine. However, the combination of eflornithine with a nitrate derivative (free radical generator) such as nifurtimox should be beneficial in terms of the toxicity of the nitrate derivatives (reduction in dosage as a result of a synergism of action).

**2. Objectives**

## Main objective

To compare the following three therapeutic combinations in terms of therapeutic efficacy and clinical safety: A: [melarsoprol + nifurtimox], B: [melarsoprol + eflornithine] et
C: [eflornithine + nifurtimox] in patients suffering from *Tbg* HAT in the meningo-encephalitic phase.

## Secondary objective

To test IgM, a biological parameter as a predictive factor for the appearance of relapses during the follow up of the patients treated. This parameter should allow for a detection faster than traditional methods such as parasitological diagnosis.

**3. Methods**

**3.1. Study design**

Open, randomised, clinical equivalence trial

**3.2. Study population**

The study will be undertaken in the HAT treatment centre of Arua in Northern Uganda.

## Inclusion criteria

All patients suffering from *Tbg* HAT, with the following criteria:

- confirmed second-stage *T.b. gambiense* infection :
- Infection diagnosed parasitologically (blood or lymph node fluid) and white blood cells > 5/mm3 in cerebrospinal fluid (CSF)
- or Trypanosomes detected in the CSF [[1]](#footnote-2) with any CSF cell count
- and resident in the district
- and written consent of the patient or of one of the parents/guardians for children under 15 years of age.

The laboratory tests must have been carried out within the previous 14 days to be valid.

***Exclusion criteria***

Any patients suffering from *Tbg* HAT admitted for treatment will be excluded from the study if one of the following criteria is met:

- Confirmed first-stage *T.b. gambiense* infection :
- Infection diagnosed parasitologically (blood or lymph node fluid) and trypanosomes not detected in the cerebrospinal fluid (CSF)
- and White blood cells £5/mm3 in CSF
- Second-stage *T.b. gambiense* infection :
- Trypanosome absent from blood (or lymph node fluid) and from CSF
- Or women pregnant on inclusion
- Or previous history of HAT confirmed treated during the last 24 months
- Or impossibility of regular access to the treatment centre during the 2 years following the end of the treatment
- Or less than 10 kg of body weight
- Or refugee patient

Patients diagnosed but non included in this protocol will be treated in accordance with the Uganda National Sleeping Sickness Control Programme protocols.

## Timetable

The decision to include a patient will be taken at the time of admission (D1). Patients included in the study will be monitored during their hospitalisation and the 2 years following the end of the treatment. At the end of hospitalisation, all patients will receive a timetable with all their control appointments.

**3.3. Sample size**

## Null hypothesis

The difference in the cure rates between 2 groups obtained during the treatment of patients in the meningo-encephalitic phase is greater than 10%.

## Alternative hypothesis

The difference in the cure rates between 2 groups obtained during the treatment of patients in the meningo-encephalitic phase is less than or equal to 10%.

If the observed difference in cure rates between the 2 groups is less than 10%, the null hypothesis will be rejected and the two treatments will be considered equivalent. The risk of error will then be 5% (alpha error) because if the difference in actual cure rates between the 2 treatments is greater than 10%, there is a 95% chance of demonstrating it (alpha error). Conversely, if the observed difference in the observed cure rates between the two groups is greater than 10%, the null hypothesis will not be rejected and the 2 treatments will be considered different, at a beta error set at 20%. The allocation ratio will be uniform (1 patient in group A to 1 patient in group B to 1 patient in group C).

Assuming a 95% cure rate, a maximum difference in cure rates between the groups of 10%, an identical drop-out rate in the 3 groups, an alpha error of 5% (one-sided test) and a power of 80%, this yields a sample size of 130 patients to be included in each group, i.e. 390 patients in the study. Allowing for a 10% drop-out rate, a final figure of 145 patients per group is obtained, i.e. 435 patients in total.

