## Multivariate analysis

Certain clinical and laboratory variables might be confounding factors, which must be taken into account during the analysis. Cox’s model (proportional hazard) will be used to obtain an estimate of the relative risk adjusted for these variables.

In an equivalence study, the point of interest is the difference observed between the two groups, assuming a 90% confidence interval (or an upper limit of 95%) around this difference (with a one-tailed test):

- If the upper limit is above 10%, the null hypothesis that there is a difference between the 2 groups cannot be rejected. If B is compared with A, it will be concluded that B is superior to A (at the 20% level).
- If the upper limit is below 0%, it will be concluded that A is superior to B (at the 20% level).
- Finally, if the upper limit is between 0 and 10%, the null hypothesis may be rejected and the alternative hypothesis accepted that the 2 groups A and B are equivalent (at the 5% level).

In the same way, for the analysis of survival, a 90% confidence interval (or an upper limit of 95%) is set around the relative hazard:

- If the upper limit is above a relative hazard of 1.12 (0.95/0.85) (i.e. 1.12 times more risk of treatment failure during the 24 months following treatment in one group than in the other), the null hypothesis that there is a difference between the 2 groups cannot be rejected.
- If the upper limit is below 1.0, it will be concluded that A is superior to B (at the 20% level).
- Finally, if the upper limit is between 1.0 and 1.12, the null hypothesis may be rejected and the alternative hypothesis accepted that the two groups A and B are equivalent (at the 5% level).

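### Section 3.3 declares equivalence whenever the observed difference is below 10% and calls the error 5%; at the margin it is about 46 to 50%, and section 3.8 states a different rule

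*Protocol*

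**What the plan says.** Protocol section 3.3 (Sample size) sets the null hypothesis as a true difference in cure rates above 10% and the alternative as a difference of 10% or less. Under the heading Alternative hypothesis it gives the decision rule: "If the observed difference in cure rates between the 2 groups is less than 10%, the null hypothesis will be rejected", after which the two treatments count as equivalent. The next sentence begins "The risk of error will then be 5% (alpha error" and justifies this by a 95% chance of detecting an actual difference above 10%. The rule is then repeated in reverse: an observed difference above 10% means that the null hypothesis stands and the treatments are considered different. The design assumes a 95% cure rate, a 10-point margin, a one-sided alpha of 5% and 80% power, and "this yields a sample size of 130 patients to be included in each group, i.e. 390 patients in the study". A 10% drop-out allowance raises this to 145 per group.

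Protocol section 3.8 (Analysis), under the heading Multivariate analysis, states a different rule: "the point of interest is the difference observed between the two groups, assuming a 90% confidence interval", or equivalently a one-sided 95% upper limit. An upper limit above 10% means that the null hypothesis cannot be rejected. An upper limit between 0 and 10% means equivalence at the 5% level. An upper limit below 0 is read as superiority of one group.

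**The concern.** Comparing the observed difference itself with the margin takes no account of sampling error. If the true difference is exactly 10 points, the observed difference is centred on 10 and falls below it about half the time, at any sample size. The 5% that section 3.3 attaches to this rule belongs to a rule based on a confidence limit, which is a different decision.

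The primary efficacy conclusion is at stake. This is an open trial with three pairwise comparisons, each of which could end in a statement of equivalence. Two written rules can disagree on the same data, and the more lenient one lacks the error control claimed for it.

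**Working it through.** **Inputs, all from the protocol.** Cure rate 95% and margin 10 points, so the boundary case is 95% vs 85%; section 3.8 uses the same pair (0.95/0.85) for its relative-hazard limit. One-sided alpha 5%, power 80%, 130 per group, 145 with drop-out.

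**1. The planned sample size reproduces.** A one-sided two-proportion formula for 95% vs 85% (mean 0.90) gives

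n0 = [1.645 × √(2 × 0.90 × 0.10) + 0.842 × √(0.95 × 0.05 + 0.85 × 0.15)]² / 0.10² = 110.2.

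With continuity correction, n = (n0/4) × [1 + √(1 + 4/(n0 × 0.10))]² = 129.5, rounded up to 130. Then 130/0.90 = 144.4, rounded up to 145. Both figures match.

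**2. Error of the section 3.3 rule.** The probability of an observed difference below 10 points in absolute value was found by exact enumeration of two independent binomials.

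| True cure rates | 130 per group | 145 per group |
|---|---|---|
| 95% vs 85% | 46.2% | 50.4% |
| 95% vs 83% | 26.7% | 29.1% |
| 95% vs 80% | 8.7% | 9.2% |

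At 130 per group a difference of exactly 10 points (13 patients) is possible. Counting it as equivalent raises the first figure to 54.6%.

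**3. What a 5% error would require.** At 95% vs 85% with 130 per group, the standard error is √((0.0475 + 0.1275)/130) = 0.0367. The critical observed difference is 0.10 − 1.645 × 0.0367 = 0.040, about 4 points rather than 10.

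**4. Where the two rules part.** Take 130 per group, a Wald limit, and the difference running in the direction that the upper limit tests. With 4 to 9 failures in the better group, the upper limit stays below 10% only for observed differences up to 3.8 to 4.6 points (5 or 6 patients). For example, observed rates of 95% and 88% differ by 7 points; the standard error is √((0.0475 + 0.1056)/130) = 0.0343 and the upper limit is 7 + 1.645 × 3.43 = 12.6 points. Section 3.3 calls this equivalent and section 3.8 does not. In this direction the two rules give different answers on equivalence in about 46% of trials at true rates of 95% vs 90%, and about 41% at 95% vs 85%.

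**5. Direction matters in section 3.8.** Reversing the sign of the same 7-point difference gives an upper limit of −7 + 5.6 = −1.4, which section 3.8 reads as superiority. Observed rates of 95% and 90% give an upper limit of 5 + 1.645 × 3.25 = 10.3 points one way, so the null hypothesis is not rejected. The other way it is −5 + 5.3 = +0.3, which is equivalence.

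**6. Candidate single rule.** If both 90% limits must lie within ±10 points, then at 130 per group the probability of declaring equivalence is 5.6% at 95% vs 85%, 1.8% at 95% vs 83%, 0.2% at 95% vs 80%, and 94.8% when both true rates are 95%.

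**The case against.** The best defence is that section 3.3 is explanatory text for a sample-size calculation, that the operative rule is in section 3.8, and that the stated 5% fits that rule (5.6% exact at 95% vs 85% in the direction tested). On this reading section 3.3 only paraphrases loosely. Part of this stands: an interval rule is in the protocol, and an analyst may well follow it. But section 3.3 states the point-estimate rule twice, distinguishes observed from actual cure rates, and attaches the 5% directly to the observed-difference rule. Nothing gives section 3.8 precedence, and its rule sits under a heading on multivariate analysis.

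Three stronger readings are tempting and are not supported.

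- A reader might infer that any pair of groups 4 to 10 points apart fails equivalence under section 3.8. That section uses only the upper limit, so the same gap in the other direction can be called equivalent or superior. The 4-point threshold also holds only near 95% vs 85%; at 85% vs 75% the standard error is about 0.049 and the threshold about 1.9 points.
- A reader might infer that section 3.8 as written holds the error near 5% in both directions. It does not. When a true 10-point gap runs the other way, it declares equivalence in 12.6% of trials at 95%/85% and 34% at 85%/75%, with 130 per group. The 5.6%, 1.8% and 0.2% in step 6 describe the proposed two-limit rule.
- A reader might infer that the trial is too small. The planned figures reproduce, and power under a confidence-interval rule is ample.

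**Conclusion.** The decision rule in section 3.3 is wrong as written. Its false-equivalence risk at the margin is about 46% at 130 per group and 50% at 145, against the 5% claimed, and it still exceeds 5% at a true difference of 15 points. It also conflicts with section 3.8 over observed differences from about 4 or 5 to just under 10 points, near 95% vs 85% and in the direction that the upper limit tests. The protocol does not say which rule applies.

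The figures assume independent binomial outcomes, equal groups, full evaluability at the stated sizes and, for the interval rules, Wald limits. They apply to one pairwise comparison. The fault must be corrected because it concerns the primary conclusion. It lies in the rule and its error statement, not in the sample size.

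**What to change.** In section 3.3, replace the observed-difference rule with: *equivalence is concluded only if the two-sided 90% confidence interval for the difference in cure rates lies wholly between -10 and +10 points*. Attach the 5% error to that rule, and delete the statement that an observed difference above 10% means the treatments are different.

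In section 3.8, change the equivalence bullet for the difference to the same two-limit rule. Editing section 3.3 alone would leave a two-limit rule there against an upper-limit rule in section 3.8, and so would not remove the contradiction. The superiority bullets in section 3.8 are a separate matter, but should be read against the new wording.

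The cost is a few sentences in two sections. At 130 per group the two-limit rule has about 95% power if both true cure rates are 95%, so the planned 130 and 145 per group can stand.

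### The 130 per group is the size for detecting 95% versus 85% cure, so the stated 80% is not the power of the planned equivalence test

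*Protocol*

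**What the plan says.** Protocol section 3.1 describes the design as "Open, randomised, clinical equivalence trial". Section 3.3 gives the null hypothesis as "The difference in the cure rates between 2 groups obtained during the treatment of patients in the meningo-encephalitic phase is greater than 10" per cent; the alternative is a difference of at most 10%.

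The sample size paragraph in section 3.3 lists its inputs as follows: "Assuming a 95% cure rate", "a maximum difference in cure rates between the groups of 10" percentage points, and "an alpha error of 5% (one-sided test) and a power of 80" per cent. It concludes that "this yields a sample size of 130 patients to be included in each group, i.e. 390 patients in the study". A 10% drop-out allowance then raises this to 145 per group, 435 in all. No formula is named, and no true difference under the alternative is given.

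Section 3.8 (under Multivariate analysis) tests equivalence by setting a 90% confidence interval, or a 95% upper limit, against 10%. For the hazard ratio limit it writes the contrast as 0.95/0.85.

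Two other places bear on the assumed cure rate. Section 1.2 reports that "In Arua in north-west Uganda, about 25% of cases of HAT treated for the first time with a complete course of melarsoprol" fail treatment, and section 3.2 says: "The study will be undertaken in the HAT treatment centre of Arua in Northern Uganda".

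**The concern.** An equivalence test and a test for a difference have opposite null hypotheses, and the same inputs give them different sample sizes. Section 3.3 presents 130 as the size that gives 80% power to reject a difference above 10 points. If 130 comes from the calculation for detecting a 10-point difference, the 80% describes a test the trial will not run.

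The power of the planned test then appears nowhere in the protocol. It depends steeply on the common cure rate, because the variance of a proportion grows quickly as the rate moves down from 95%. A reader relying on 80% would understate the power if cure is near 95% and, on the two-limit reading, overstate it once cure is below about 92%. This matters when a pairwise comparison fails to show equivalence: section 3.3 would call the two treatments different, when low power might be the reason.

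**Working it through.** **Inputs (section 3.3).** Cure rate 0.95; limit 0.10; one-sided alpha 0.05 (z = 1.645); power 0.80 (z = 0.842); equal allocation. The second rate, 0.85, is 0.95 minus 0.10 and also appears in section 3.8.

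**Step 1: reproduce 130.** One-sided test for a difference, 0.95 versus 0.85, mean rate 0.90:

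n = [1.645 × √(2 × 0.90 × 0.10) + 0.842 × √(0.95 × 0.05 + 0.85 × 0.15)]² / 0.10²
= [1.645 × 0.4243 + 0.842 × 0.4183]² / 0.01 = 110.2

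With continuity correction: n′ = (110.2/4) × [1 + √(1 + 4/(110.2 × 0.10))]² = 129.5, so 130.
Drop-out: 130/0.90 = 144.4, so 145. Both stated figures are matched.

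**Step 2: equivalence formulas with the same inputs.** Common rate 0.95, so 2 × 0.95 × 0.05 = 0.095.

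- One limit: (1.645 + 0.842)² × 0.095/0.01 = 58.7, so 59.
- Both limits (beta halved, z = 1.282): (1.645 + 1.282)² × 0.095/0.01 = 81.4, so 82.
- With continuity correction: 78 and 101.
- Farrington-Manning: 78 and 103.
- Null variance at 0.95/0.85 with alternative variance at 0.95/0.95: 90 and 118 (109 and 137 with correction).

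None gives 130 at the stated alpha and power. Routes to 128 or 129 exist, but they need something the protocol does not state (an alpha of 2.5% or 0.05/6), or they put the 0.95/0.85 variance in both terms.

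**Step 3: power of the planned test with 130 evaluable per group and no true difference.**

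SE = √(2p(1 − p)/130); one-limit power = Φ(0.10/SE − 1.645); two-limit power = 2Φ(0.10/SE − 1.645) − 1.

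At p = 0.95: SE = 0.02703, 0.10/SE = 3.699, Φ(2.054) = 0.980, and 2 × 0.980 − 1 = 0.960.

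| Common cure rate | Two limits | One limit |
|---|---|---|
| 95% | 96.0% (exact 94.8%) | 98.0% (exact 97.4%) |
| 92% | 81.5% (exact 80.5%) | 90.8% (exact 90.3%) |
| 90% | 70% | 85% |
| 85% | 46% | 73% |
| 75% (sensitivity case only) | 17% | 59% |

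The exact figures enumerate both binomial distributions and apply the Wald 90% interval rule.

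**Step 4: effect of a true difference.** With 95% cure in one arm, one-limit power = Φ((0.10 − δ)/SE − 1.645), where SE uses both rates. This gives 86% at δ = 2 points, 80% at 2.5 points and 74% at 3 points.

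**Step 5: exact power at the smaller sizes.** The Wald 90% interval rule at 95% cure gives 79.3% for 59 per group (one limit) and 78.1% for 82 per group (two limits).

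**The case against.** The strongest reply is that the arithmetic is sound. A standard formula fed with the four stated inputs gives 130 and then 145, and no other formula is named. That stands: the fault lies in the choice of formula for the hypothesis, not in a miscalculation. That this formula was the one used is an inference, though the match is exact.

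Second, no single figure is the true power. It depends on the true difference and on one limit or two, and the protocol fixes neither clearly: it speaks of a one-sided test and an upper limit but also of a 90% interval. At 95% cure, a true difference of about 2.5 points would bring one-limit power to 80%. This also stands, and it is why power is given above as a range with conditions. But the protocol states no such difference, so it cannot be read as the basis for 130.

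Third, at the assumed 95% the mismatch is conservative. That is true. A reader might infer that the trial is oversized and that 59 or 82 per group would suffice. The check does not support this: exact power at those sizes falls just short of 80%, and those figures come from the simplest variance formula and assume no true difference.

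A reader might also infer from section 1.2 that real power in Arua is 17%. The documents do not support that either. The 25% failure rate concerns melarsoprol alone, whereas the trial tests combinations. Arm C contains no melarsoprol, so a shared 75% is relevant mainly to A versus B. Section 1.4 reports no relapse at 12 months among 69 patients given nifurtimox plus melarsoprol elsewhere, with one death. That follow-up is shorter and in another country, but it is some support for a high cure rate.

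**Conclusion.** The point holds: the 80% attached to 130 per group is not the power of the equivalence test set out in sections 3.3 and 3.8. Under the protocol's own 95%, and with no true difference, power is about 95-96% (both limits) or 97-98% (one limit). Two-limit power reaches 80% at roughly 92% cure and drops to 46% at 85%; one-limit power is still 73% there.

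These are per-pair figures for 130 evaluable patients per group. They rest on equal true cure rates and the 90% interval rule. The sample size itself need not change on this account. What is wrong is the stated derivation and the power claimed for it.

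**What to change.** Keep 145 per group. In section 3.3:

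- Replace the derivation with one that matches the equivalence test, stating the true difference assumed and whether one or both limits must lie within 10 points.
- Restate the power of 130 evaluable per group under those conditions. With no true difference this is about 95-96% (two limits) or 97-98% (one limit) at 95% cure, with the figures at 92%, 90% and 85% beside it.
- If 75% cure in both arms is shown (17% two limits, 59% one limit), label it a sensitivity case relevant mainly to A versus B, and cite both the Arua figure in section 1.2 and the combination series in section 1.4.
- Do not write that 59 or 82 per group would be enough.

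The cost is a text correction. Recruitment, treatment, the 10-point limit and the analysis method are unaffected.
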